### Anthropometric measurements

At days 1 and 41 of each treatment period, body weight and waist and hip circumferences will be measured following standardized procedures. Body composition will also be assessed by dual x-ray absorptiometry (DXA) scan at the first day of the first phase and day 41 of each treatment period (in total four times during the study) to look at potential changes in body fat and lean mass composition. For this procedure, the participant will need to lie in a horizontal position for about 5–15 min while the scan arm passes from the head to the feet.

### Blood biochemical measurements

Serum samples will be analyzed for the following: fasting lipid profiles including total cholesterol (TC), high-density lipoprotein (HDL-C), low-density lipoprotein (LDL-C) and triglyceride (TG) levels, as well as, glucose, serum creatinine, blood urea nitrogen (BUN), aspartate aminotransferase (AST), alanine aminotransferase (ALT), gamma-glutamyl transferase (GGT), serum total protein and serum albumin will be measured using the automated enzymatic methods on a cobas c 311 analyzer (Roche Diagnostics, Indianapolis, IN, USA). Fasting plasma insulin concentrations will be determined using radioimmunoassay (RIA) (EMDMillipore, Etobicoke, ON, Canada) [54]. Insulin homeostasis modelling assessment (HOMA) will be utilized as an estimate for % β-cell function and insulin resistance (IR) [55].

ACE activity in the plasma will be measured by a spectrophotometric method using FAPGG as substrate [25]. Serum angiotensin II, serum aldosterone, renin, epinephrine and norepinephrine will be measured by commercial enzyme-linked immunosorbent assays (ELISA). NO concentrations will be determined in plasma using a colorimetric kit (Nitric oxide assay, Thermoscientific, Waltham, MA, USA) [56].

### Urine biochemical measurements

Twenty-four-hour urinary sodium, potassium, creatinine, magnesium, total protein and albumin will be measured on a cobas c 311 analyzer, (Roche Diagnostics, Indianapolis, IN, USA). NO concentrations will be determined in urine using a colorimetric kit (Nitric oxide assay, Thermoscientific, Waltham, MA, USA). Urinary epinephrine and norepinephrine concentrations will be measured by ELISA.

### Statistical analysis

Statistical analysis will be performed in an intent-to-treat fashion. In addition, a per-protocol analysis will also be performed to check for potential effect attenuation due to unequal compliance or protocol deviations across treatments. Statistical analysis will be performed using SAS 9.4. The endpoint of treatments and baselines will be compared using a mixed-model analysis of variance. Sequence and sex will be included as fixed factors, and participant will be included as a random factor, with participant repeated by period.

Dunnett’s test will be used to adjust for multiple comparisons with the endpoint of the baselines set as the control. Effects of treatment by time on measures repeated during treatments will be assessed using a mixed-model analysis of variance with sequence, sex, time as fixed factors and participants included as random factors, with participants repeated by period, with Tukey-Kramer adjustments for multiple comparisons. Model residuals will be visually inspected to assess independence, normal distribution, and constant variance. Datasets with residuals determined to violate these assumptions will be transformed prior to re-analysis. Results will be expressed as estimated least square means ± standard error of the mean (SEM) for all values. Statistical significance will be set at *p* < 0.05 for all analyses.

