### Sample size

A total sample size of 30 participants was calculated as required to detect a change in 4 mmHg in SBP with the proposed crossover design, using an estimated within-participant standard deviation of 5.45 mmHg and a power of 0.80 and *α* = 0.05 [13]. A recruitment goal of 35 participants has been set to account for the potential participant drop out.

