### Outcomes and measurement tools

The primary outcome of this trial will be 24-h SBP, measured at the first day of the first phase and day 41 of each treatment phase using ambulatory BP monitors (ABPM, OnTrak, Spacelabs Healthcare Inc., Snoqualmie, WA, USA) [50, 51]. Participants will be fitted with an ABPM to wear for a full day. Continuous and SBP and DBP measured over 24 h will be recorded.

Office-measured BP, pulse-wave velocity and augmentation index will be determined using an automated oscillometric measurement device (Mobil-O-Graph, IEM, Stolberg, Germany) in an office setting at days 1 and 41 of each treatment phase [52, 53]. Office-measured BP will also be measured at day 22 to track the changes at the midpoint of each treatment phase. This measurement will take place in a quiet room while the participant is in a seated position with their arm resting on an arm rest at heart level. Participants will be advised to rest quietly throughout the measurements. Oscillometric measurement will be performed four times at 2-min intervals. The first measurement will be discarded, and the last three measurements will be averaged to determine office-measured BP. The LCD display of the oscillometric measurement device will be covered so that the participant is blinded to the BP values during the measurements. BP results will not be shared with participants until they have completed the trial.

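### Between-treatment tests for secondary outcomes measured on day 1 of every period do not adjust for that day-1 value, so they are less precise than the data allow

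*Protocol article*

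**What the plan says.** Several secondary outcomes have their own starting value in each period. Under Outcomes and measurement tools, office blood pressure, pulse-wave velocity and augmentation index are taken "in an office setting at days 1 and 41 of each treatment phase", with an extra office blood pressure reading at day 22. Under Anthropometric measurements: "At days 1 and 41 of each treatment period, body weight and waist and hip circumferences will be measured". Under Sample collection, fasting blood is drawn on day 1 and on days 41 and 42 of every period.

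The Statistical analysis section describes two models.

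- The first compares treatment endpoints and baselines, with Dunnett's test and baseline as the control.
- The second is for outcomes measured repeatedly within a period: "Effects of treatment by time on measures repeated during treatments will be assessed using a mixed-model analysis of variance". Sequence, sex and time are its fixed factors, participant is random and repeated by period, and Tukey-Kramer is the multiplicity adjustment.

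Treatment is not in the second model's list of factors, although its effect by time is what is tested. Neither model has a day-1 covariate. The only covariate adjustment mentioned elsewhere (Study design, Discussion) is for body-weight change.

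The primary outcome, 24-h SBP, has a day-1 value in the first phase only. So do DXA and 24-h urine. This point does not concern them.

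**The concern.** In a crossover each participant already serves as his or her own control. A day-1 value in each period can still help, because it captures drift within the participant from one period to the next. It helps most as a covariate, where the data decide how much weight it gets. If it is instead treated as one more response and the test is a difference of changes, it is subtracted with weight 1 whatever its correlation with day 41. At low correlation that adds more noise than it removes. If only day-41 means are compared, the day-1 information is left unused.

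At stake is the precision of the secondary comparisons between products. Among them are plasma NO and ACE activity, which carry the mechanistic predictions under Anticipated results and conclusion, and office blood pressure, the secondary measure closest to the primary outcome.

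**Working it through.** **The plan's own figure.** The Sample size section states: "A total sample size of 30 participants was calculated as required to detect a change in 4 mmHg in SBP", "using an estimated within-participant standard deviation of 5.45 mmHg", with "a power of 0.80 and *α* = 0.05". Taking the test as two-sided and the variance of a paired difference as 2 × 5.45²:

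n = 2 × [5.45 × (1.960 + 0.842) / 4]² = 29.14, rounded up to 30.

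The stated 30 is reproduced; normal-approximation power at 30 is 0.81. These inputs belong to the primary outcome. They are borrowed below for illustration only and say nothing about pulse-wave velocity, lipids or weight.

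**Three possible contrasts.** Let s be the within-participant SD, assumed equal on day 1 and day 41, and r the correlation defined by day-1 and day-41 values within a period once the participant effect is removed. For one pair of treatments, the variance per participant is:

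- difference of changes (treatment by time): 4s²(1 − r)
- day 41 alone: 2s²
- day 41 adjusted for day 1: 2s²(1 − r²)

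**Reading A: differences of change are tested.** Change over adjusted = 4(1 − r) / [2(1 − r²)] = 2/(1 + r), which exceeds 1 for every r below 1. With 30 participants, s = 5.45 and a 4 mmHg difference, two-sided 0.05 and no multiplicity adjustment:

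| r (assumed) | 2/(1+r) | SE, change | SE, adjusted | Power, change | Power, adjusted |
|---|---|---|---|---|---|
| 0 | 2.00 | 1.99 | 1.41 | 0.52 | 0.81 |
| 0.3 | 1.54 | 1.67 | 1.34 | 0.67 | 0.85 |
| 0.5 | 1.33 | 1.41 | 1.22 | 0.81 | 0.91 |
| 0.7 | 1.18 | 1.09 | 1.00 | 0.96 | 0.98 |
| 0.9 | 1.05 | 0.63 | 0.61 | 1.00 | 1.00 |

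Example at r = 0.3: change SE = √(4 × 29.70 × 0.7 / 30) = 1.67; adjusted SE = √(2 × 29.70 × 0.91 / 30) = 1.34.

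The change contrast is less precise than day 41 alone only when 4(1 − r) > 2, that is, when r < 0.5.

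**Reading B: Tukey-Kramer compares day-41 cell means.** The variance is then 2s², and the share forgone by not adjusting is r²: 0%, 9%, 25% and 49% at r = 0, 0.3, 0.5 and 0.7.

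Adjusting over all treatment-by-time cells costs more. With 200 degrees of freedom assumed, the Tukey critical value is 2.88 for six cells (three products, two days) and 3.14 for nine (office blood pressure, with day 22). For three treatment pairs it is 2.36. Intervals are wider by 2.88/2.36 = 1.22 and 3.14/2.36 = 1.33 times.

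**Simulation check.** The six-sequence, three-period design with 30 participants (4,000 trials per r) gave these SEs for change / day 41 alone / adjusted:

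- r = 0: 2.01 / 1.42 / 1.43
- r = 0.3: 1.66 / 1.42 / 1.36
- r = 0.5: 1.40 / 1.40 / 1.23
- r = 0.7: 1.08 / 1.40 / 1.01

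These agree with the formulas. The cost of estimating an unneeded slope at r = 0 is 1.43/1.42, about 1%.

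**The case against.** The strongest reply is that the protocol never says differences of change are tested. It speaks of effects of treatment by time, and reports least square means rather than changes. Tukey-Kramer on such a model can compare products at day 41 directly. This stands. A reader might infer that the plan doubles the variance of its secondary comparisons, but the text does not establish that. Under Reading B nothing is lost at r = 0 except through the multiplicity adjustment. What survives is that neither reading uses day 1 as a covariate, and the text does not settle which applies.

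The first model is not expressly confined to the primary outcome, so the plan is not limited to treatment-by-time tests. That is true, but its Dunnett control is baseline, so it gives no day-1-adjusted comparison between products.

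The protocol gives no r, and at high r the loss under Reading A is trivial. This also stands: the size is an assumption.

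A reader might suppose that adjusting for day 1 disposes of carryover after the 2-week washout. It does not. A residual effect present at day 1 enters a difference of changes with weight 1 and the adjusted comparison with weight about r, so exposure is reduced rather than removed.

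A simple covariate model can also drop a period whose day-1 value is missing, which the repeated-measures model would keep. That is a real cost and needs handling.

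Finally, a treatment-by-time mixed model is valid, it suits the day-22 reading, and covariates for secondary outcomes are often left to an analysis plan. Agreed, which is why this is an optional refinement. It is raised because the article fixes the model and its terms rather than deferring them.

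**Conclusion.** The point holds as a loss of efficiency in secondary outcomes. Under Reading A the variance is 2/(1+r) times what it could be: a large loss for r up to about 0.5 and a small one above 0.8. Under Reading B the share forgone is r², which runs the other way, plus intervals about 1.2 to 1.3 times as wide if all cells are adjusted together.

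These results assume equal variance on day 1 and day 41, and an r that the documents do not supply. The power figures also borrow the primary outcome's SD and effect and ignore multiplicity.

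A reader might go further and conclude that the secondary results would be biased or that the trial is underpowered. The documents support neither. The planned model is valid, 24-h SBP has no day-1 value in the second and third periods, and the sample size of 30 is unaffected.

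**What to change.** State in the Statistical analysis section that, for outcomes with a day-1 value in every period, the between-treatment test uses the day-41 (or day-41/42) value in the crossover mixed model, with treatment, period, sequence and sex as fixed factors and participant as random. Enter day 1 as two covariates, the participant's mean day-1 value and the period's deviation from it, so that the adjustment works within participant. Apply Tukey-Kramer to the three treatment pairs. Keep the treatment-by-time model, including day 22 for office blood pressure, to describe the time course. Say how a period with a missing day-1 value is handled so that it is not dropped.

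The cost is a few sentences and two covariates, with no new visits, samples or participants. The statistical price is about 1% in SE when r is near zero. The change should be fixed before the treatment code is broken.

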### Sample collection

Twelve-hour morning fasting (i.e., nothing to eat or drink except water 12 h prior) blood samples will be collected on the first day of each phase (baseline), and on days 41 and 42 of each treatment periods of the trial (in total nine times during the trial). This fasting blood samples (approximately 4 teaspoons or 20 ml) will be taken from the top of the forearm via venipuncture by a phlebotomist on each blood-draw day for assessment of blood biochemical markers. Each blood test will take approximately 5 min. No alcoholic beverages are to be consumed within 48 h prior to blood draws during the study periods. No food or caffeinated beverage consumption is allowed within 12 h prior to blood draws during the study periods. Blood samples will be centrifuged at 3000 rpm for 20 min at 4 °C, aliquoted to yield serum, plasma and RBCs, and then stored at − 80 °C until analyses.

Participants will be asked to collect 24-h urine samples at the first day of first phase and last day of each treatment period. Urine containers will be kept in the fridge during the day of collection, and then will be aliquoted and stored at − 80 °C until analyses. The volume of the 24-h urine samples and start and end time of collection will be recorded.

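### The treatment-by-time model carries a period-level repeat clause although its measures repeat by day within a period; on its natural reading, any within-period correlation goes unmodelled for these secondary measures

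*Protocol article*

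**What the plan says.** The Statistical analysis section of the protocol article describes two mixed models.

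- **Endpoint model.** It compares end-of-treatment values and baselines, with the structure "participant will be included as a random factor, with participant repeated by period".
- **Treatment-by-time model.** It is introduced as "Effects of treatment by time on measures repeated during treatments will be assessed using a mixed-model analysis of variance". The effects it lists are "with sequence, sex, time as fixed factors". Its covariance clause reads "participants included as random factors, with participants repeated by period, with Tukey-Kramer adjustments for multiple comparisons".

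The two models therefore share the same covariance clause. No covariance type, day-level repeat or participant-by-period term is named for the second.

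The measurement schedules are given elsewhere in the article:

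- **24-h systolic pressure (primary)**, Outcomes and measurement tools: "measured at the first day of the first phase and day 41 of each treatment phase". That is one value per period plus one baseline.
- **Office blood pressure, pulse-wave velocity, augmentation index**, same section: "in an office setting at days 1 and 41 of each treatment phase".
- **Office blood pressure, extra reading**, same section: "Office-measured BP will also be measured at day 22 to track the changes at the midpoint of each treatment phase". That makes three days per period.
- **Blood markers**, Sample collection: on the first day of each phase and "on days 41 and 42 of each treatment periods of the trial (in total nine times during the trial". That makes three samples per period.

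**The concern.** In this crossover, treatment changes between periods and day changes within them. The two effects have different error variances whenever readings from the same period share something beyond the participant's own level. A model with one participant effect and one pooled residual treats days 41 and 42 of one period as no more alike than readings from periods weeks apart.

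The pooled residual is then too small for treatment means averaged over days and too large for treatment-by-time contrasts. The article makes such shared deviation plausible: its Discussion expects energy intake and body weight to shift during treatment periods and says this could move blood pressure. Office blood pressure and, if analysed this way, the nitric oxide and ACE results on which the anticipated mechanistic conclusions rest would be tested at 0.05 with this model.

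**Working it through.** **1. The plan's own figure.** The Sample size section gives a 4 mmHg difference, within-participant SD 5.45 mmHg, power 0.80 and alpha 0.05 (taken as two-sided).

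n = 2 × (5.45 × (1.960 + 0.842) / 4)² = 29.1, rounded up to 30. The plan's 30 is reproduced. It rests on one 24-h systolic value per period and does not involve the treatment-by-time model.

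**2. Inputs for the check.**

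- From the article: 30 participants, three periods, SD 5.45 mmHg, two or three days per period.
- Assumed: treatment and treatment-by-time are fitted (the listed fixed factors omit treatment, although its interaction with time is the effect under test).
- Assumed: rho, the share of within-participant variance common to readings of the same period, from 0 to 0.7.
- Assumed: the 24-h SD is borrowed for office blood pressure.

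**3. Expected mean squares, three days per period** (in units of the within-participant variance, equal correlation within a period).

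- Treatment, and participant-by-treatment (2 × 29 = 58 df): 1 + 2rho.
- Treatment-by-time, and the within-period residual (174 df): 1 - rho.
- Pooled residual (270 - 30 - 8 = 232 df): [58(1 + 2rho) + 174(1 - rho)] / 232 = 1 - 0.25rho.

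At rho 0.3 these are 1.6, 0.7 and 0.925. The treatment F is inflated by 1.6 / 0.925 = 1.73, and the treatment-by-time F is deflated to 0.7 / 0.925 = 0.76.

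**4. Two days per period.** Treatment is 1 + rho. The pooled residual has 58 + 87 = 145 df and equals [58(1 + rho) + 87(1 - rho)] / 145 = 1 - 0.2rho. At rho 0.3 the inflation is 1.3 / 0.94 = 1.38.

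**5. Simulated rejection rates and power** (4,000 trials per case). The power columns take one treatment falling linearly from 0 on day 1 to -4 mmHg on day 41, three days per period.

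| rho | Treatment means, null, 3 days | Treatment means, null, 2 days | Treatment-by-time, null, 3 days | Power, pooled residual | Power, participant-by-period term added |
|---|---|---|---|---|---|
| 0 | 5.3% | 5.3% | 4.2% | 42% | 42% |
| 0.1 | 8.1% | 7.0% | 3.7% | 40% | 46% |
| 0.3 | 16.7% | 11.3% | 1.1% | 38% | 57% |
| 0.5 | 27.0% | 15.8% | 0.4% | 34% | 74% |
| 0.7 | 36.3% | 22.7% | 0.0% | 29% | 93% |

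A separate simulation of 3,000 trials gave 18.0% for treatment means at rho 0.3 with three days; the mean squares in step 3 imply about 17.6%. With the participant-by-period term, all null rejection rates lie between 4.2% and 5.5%.

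**6. A different correlation shape.** Here correlation decays with calendar days across a 56-day cycle (42 days of treatment plus 14 of washout), still analysed with the pooled residual. Null rejection rates for a 30-day correlation of 0.2 / 0.5 / 0.8:

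| Days | Treatment means | Treatment-by-time |
|---|---|---|
| 1, 22, 41 | 15.4 / 22.9 / 29.6% | 3.8 / 1.9 / 0.5% |
| 1, 41 | 5.9 / 9.1 / 12.9% | 6.6 / 4.4 / 2.2% |
| 1, 41, 42 | 18.8 / 25.0 / 30.4% | 5.5 / 3.5 / 1.3% |

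The treatment-by-time test is conservative throughout for days 1/22/41. For the other two schedules it is near nominal when serial correlation is weak.

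**The case against.** The strongest reply is that the article never says residuals are independent. The clause could mean that participant-by-period is the block, which would model the within-period correlation and remove both consequences. Covariance details are also commonly left to an analysis plan, and this is a condensed article.

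Part of this stands: the covariance type is not fixed, so the harmful model is a reading and not a certainty. But the block reading does not fit the endpoint model. For 24-h systolic pressure a participant-by-period block holds a single value, so nothing repeats within it, and the phrase works there only with period as the index. Carried over with that meaning, it gives either independent residuals or, under a structured covariance, a singular matrix because several days share one index. The objection is to a structure the article states, not to one it leaves out. The planned visual check of residual independence does not rescue it, since the only stated remedy is transformation.

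A reader might infer more than the article supports:

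- **That every treatment-by-time test loses power.** Step 6 shows otherwise for the 1/41 and 1/41/42 schedules.
- **That treatment differences will be declared too often as planned.** The inflated comparison is the treatment mean over all days, including day 1. The named test is treatment by time, and the article does not say which contrasts receive Tukey-Kramer. A treatment comparison on a single day stays roughly calibrated: at rho 0.3 with three days, the true variance exceeds the pooled one by only 1 / 0.925 = 1.08.
- **That the loss is established.** The random participant effect already absorbs correlation common to all of a participant's readings; only the excess within a period matters, and the article gives no value for it.
- **That blood markers certainly enter this model.** Days 41 and 42 might instead supply the endpoint model. Only office blood pressure, with its day-22 reading, clearly needs the repeated-measures model.

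**Conclusion.** The concern holds in conditional form. The stated repeat clause does not match measures that repeat by day, and on its natural reading any excess within-period correlation is left out of the error term.

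If rho is above zero, treatment means across days are tested anti-conservatively and, for office blood pressure, the treatment-by-time test is conservative. At rho 0.3 that means about 17-18% rejection at nominal 5% with three days per period, about 11% with two, and power of about 38% instead of 57%. These sizes rest on the assumed rho, equal correlation within a period, the borrowed SD of 5.45 mmHg and the assumed linear effect. At rho 0 the two models agree.

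Only secondary measures are touched. The primary 24-h systolic analysis and the sample size of 30 stand. The wording should be corrected before analysis.

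**What to change.** In the treatment-by-time model, replace the period-level repeat clause with a random participant effect plus a random participant-by-period effect. Equivalently, make day the repeated factor with participant-within-period as the subject. Keep the period-level repeat only in the endpoint model, where each participant has one value per period. State which of the repeated measures (office blood pressure, pulse-wave velocity, augmentation index, blood markers) go through which model.

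The cost is one line of text and of SAS code, with no extra data or participants. The model gains one variance parameter, and treatment means are tested on fewer denominator degrees of freedom (58 instead of 232 in the balanced case above), so some of their p-values will rise.
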